## **1- Outline the theoretical, empirical and/or conceptual basis, background evidence for the research proposal with relevant literature.**

The frequency, intensity and duration of heat waves are increasing globally (Bi et al. 2011), and with these increases we can expect with a high level of certainty a parallel rise in heat-related morbidity and mortality (Hajat, O'Connor & Kosatsky, 2010). In an attempt to combat this, there is a need for evidence-based guidelines to be made available that educate people on the steps they can take to protect themselves during extreme heat events. One particular population group at a disproportionately higher risk of morbidity and mortality during these extreme weather events is the elderly (Hajat, O'Connor & Kosatsky, 2010). Therefore, it is of great importance to make targeted recommendations for this population. Air-conditioning is the best protection during extreme heat events, but it is not accessible to many of the most vulnerable populations and widespread use and reliance on it during extreme heat events can cause blackouts (Kaiser et al., 2001; Semenza et al., 1996). Researchers began examining the effectiveness of using a fan as a cooling intervention and found that public health recommendations regarding fan-use were not uniform between agencies and often not evidence-based (Jay et al., 2015). If fan-use were to be found effective, it would provide a low-cost solution with a low-energy requirement. Research to date suggests that the benefits of fans have been greatly underestimated by public health agencies (Jay et al., 2015). Despite organizations such as the WHO, EPA and the Government of Victoria advising against using fans in hot conditions, a study published in the Journal of the American Medical Association (JAMA) demonstrated that fan use reduced physiological strain in young healthy men in simulated hot/humid heat wave conditions (Ravanelli et al., 2015). The use of a fan increased airflow which improved sweating efficiency and led to greater evaporative heat loss. The effectiveness of fan-use does depend on both the unique environmental conditions and the individual; it has been suggested that in certain conditions fans may be less effective and even harmful to older adults due to age-related decrements in sweating (Gagnon et al., 2016). Due to the findings to date it is clear that there is a need for evidence based recommendations specific to both the environmental conditions and population-specific, particularly those populations who have compromised thermoregulatory ability, such as the elderly. In a recent article by Jay and Capon (2017) it was proposed that external skin wetting could be used by the elderly to compensate for their decreased sweating ability, while still gaining the benefits of increased latent heat loss as a result of improved evaporative efficiency with fan-use. This combination has the potential to be a simple, cost-effective cooling intervention that has 50-times lower cost and electricity requirement than air conditioning and so therefore can be utilized by vulnerable populations in a low-resource environment. We propose the below study to examine if fan-use, in combination with skin-wetting can be an effective cooling strategy that is able to decrease the physiological strain experienced by elderly during heat waves, and as a result decrease their chance of experiencing an adverse cardiovascular event. During the 2003 heat wave in Lyon, France, antihypertensive use was associated with a 177% increased risk of mortality in adults presenting to the emergency department with heat stroke (Argaud et al., 2007). Due to this historical evidence and the prevalence of hypertension in older adults, it is important to include older adults on antihypertensives in our study to adequately represent the older adult population, while also investigating the impact of antihypertensive use on individuals' responses to simulated heat wave exposure and the proposed interventions. We believe the proposed project will provide evidence

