An initial study in young healthy adults (20-30 years of age) was conducted to determine if fan use modifies the highest humidity that can be tolerated before increases in cardiovascular (i.e., heart rate) and thermal (i.e. core temperature) strain are observed. Compared to no fan use, the relative humidity (RH) at which cardiovascular strain occurred was ~20% RH higher with a fan at 36°C, and ~10% RH higher with a fan at 42°C (Fig. 1). Moreover, thermal strain was only observed at 36°C without a fan, and at a ~10% higher RH at 42°C with a fan (Fig. 1; right). These results demonstrate that fan use might be beneficial during heatwaves, even at high ambient temperatures of 42°C, since it delayed the point at which cardiovascular and thermal strain occurred. Since younger adults are generally not considered at risk during heat waves, we performed a follow-up study that assessed the efficacy of fan use for cooling healthy older (60-80 years) adults during a simulated heatwave at 42°C. In contrast to the findings in younger adults, we found that fan use resulted in a higher heart rate and core temperature in older individuals (Fig. 2). In this case, fan use was detrimental, an observation that is likely explained by age-related reductions in sweating capacity.

[figure not shown][figure not shown]

Two key findings emerge from these studies; a) fan use has clear protective potential in young healthy people even at temperatures that far exceed the current public health guidelines (e.g. WHO); and b) the efficacy of fan use for cooling is dependent on the ability to physiologically wet the skin and as such fans become detrimental when used alone in older individuals because of impairments in sweating that occur with ageing. It stands to reason, however, that age-related reductions in sweating can be compensated in older individuals by simply applying water to the skin surface. This would in turn greatly increase the cooling effect of fan use. Since heat loss capacity will likely be most limited in CAD patients prescribed beta-blockers secondary to a blunted skin blood flow, the benefits of skin wetting with fan use may be most pronounced in this group during heatwave conditions. However, the efficacy of skin wetting with or without fan use

to alleviate thermal and/or cardiovascular strain of CAD patients during heat waves has not been evaluated.

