## 6- Statistics

### 6.1 Sample size

The sample size computation is based on comparison of the primary endpoint (change in rate pressure product from baseline to the end of a 3 hour simulated heatwave exposure to 38°C and

60% RH) between the 4 conditions of control, fan use alone, skin wetting alone, fan use + skin wetting.

The mean and standard deviation of the change in rate pressure product were taken from the preliminary data presented in Figure 3 and are expected to range between 1000 bpm x mmHg and 1700 bpm x mmHg for the mean and between 1700 bpm x mmHg and 2000 bpm x mmHg for the standard deviation. The standard deviation of the difference between conditions is expected to be similar.

The main interest is to compare the control condition with the 3 other conditions taken individually, which implies a significance level of 0.0167 ( $0.05 / 3$ ). A difference of 1250 bpm x mmHg in change in rate pressure product between the control condition and any other condition is judged to be clinically relevant.

In this context a sample size of 30 participants will give 80% power to detect a difference of 1250 bpm x mmHg in change between the control condition and any other condition, assuming that the standard deviation of the difference between conditions is 2000 bpm x mmHg and using a paired t-test with a 0.0167 two-sided significant level. To account for an approximately 10% loss to follow-up rate, 34 participants will be included in the study. Of the 34 participants, 17 will be taking beta-blockers whereas the other 17 will not be taking beta-blockers.

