#### 5.2.1 Primary Analysis

The following descriptive statistics will be presented for the primary endpoint (change from baseline in rate pressure product) under the 38°C and 60% RH heatwave exposure: mean, standard deviation, median, Q1, Q3, minimum and maximum.

A restricted maximum likelihood (REML)-based linear mixed model including a term for condition and accounting for repeated measures, will be used to compare the change from baseline in rate pressure product under the 38°C and 60% RH heatwave exposure under the following conditions: control, fan alone, skin wetting alone and fan + skin wetting. Contrasts under this model will allow for the three main comparisons:

- Control vs. fan alone
- Control vs. skin wetting alone
- Control vs. fan + skin wetting

Differences between the control condition and each of the 3 other conditions will be tested and presented with point estimate along with 98.33% confidence intervals. These three comparisons will be tested at the 0.0167 significance level to control for the multiplicity of tests.

The assumption of normality underlying this model will be checked.

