### 5.2.2 Secondary Analysis

Descriptive statistics (mean, standard deviation, median, Q1, Q3, minimum and maximum) will be presented for the change in rate pressure product from baseline to end of a 3-hour simulated heatwave exposure at 45°C and 15% RH. The change in rate pressure product will be analyzed using a REML-based linear mixed model including a term for condition and accounting for repeated measures. Contrasts under this model will allow for the three following comparisons:

- Control vs. fan alone
- Control vs. skin wetting alone
- Control vs. fan + skin wetting

The difference between the control condition and each of the 3 other conditions will be presented with point estimate along with 95% confidence intervals.

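### SAP 5.2.1 plans only contrasts with control, so it gives no interval or test for what a fan adds once the skin is wet, or for whether wetting changes the fan's effect

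*Supplement*

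**What the plan says.** SAP 5.2.1 compares the change in rate pressure product at 38°C/60% RH across "control, fan alone, skin wetting alone and fan + skin wetting". The model is a REML mixed model "including a term for condition and accounting for repeated measures". The SAP continues: "Contrasts under this model will allow for the three main comparisons", and lists control against each of the other conditions. It then states: "Differences between the control condition and each of the 3 other conditions will be tested", at 0.0167 each with 98.33% intervals. SAP 5.2.2 does the same at 45°C/15% RH ("Contrasts under this model will allow for the three following comparisons"), with 95% intervals.

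The interactions that the SAP does plan are condition by beta-blocker (5.2.3), by sex and by site (5.2.4), and by season (5.2.5). No section plans a fan by wetting interaction or a comparison of fan + wetting with wetting.

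The background sections reason about how the two measures combine. The Montreal protocol (section 2, literature review) says of wetting older people's skin: "This would in turn greatly increase the cooling effect of fan use". The Sydney protocol (section 1) cites a proposal that "external skin wetting could be used by the elderly to compensate for their decreased sweating ability" while the benefit of the fan is kept. SAP 2.2 sets the objective of finding the best cooling strategy. Its hypothesis is narrower: control gives a greater rise than each of the three interventions.

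**The concern.** Two questions follow from this design and this rationale. The first is practical: once the skin is wet, does a fan add anything? That is fan + wetting versus wetting. The second is the one in the Montreal literature review: does wetting change what the fan does? That is a difference of differences, (fan + wetting − wetting) − (fan − control).

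Control versus fan + wetting answers neither, because it combines wetting's own effect with whatever the fan adds. Suppose fan alone is not significant and fan + wetting is. A reader could easily conclude that wetting makes the fan work, yet the same pattern appears when the fan is inert and wetting does everything. The results are meant to inform public-health advice on fans, so the distinction matters.

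**Working it through.** **Inputs**
- SD of the within-person difference 2000, relevant difference 1250, and "using a paired t-test with a 0.0167 two-sided significant level" (Montreal protocol 6.1).
- Completers: 30 in Montreal (6.1) and 45 in Sydney (4.4). The SAP pools the sites but gives no total, so n = 30 + 45 = 75 is an assumption.
- Equal SD for every pairwise difference (compound symmetry) is also an assumption.

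**The plan's own figure.** A paired t-test with difference 1250, SD 2000 and two-sided 0.0167 needs n = 30, with power 80.5%. Allowing 10% loss, 30/0.9 = 33.3, so 34. Both figures reproduce.

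**Precision of the omitted contrasts**
- Fan + wetting versus wetting: SD 2000, the same as a control contrast. At n = 75, SE = 2000/√75 = 231. The 95% half-width is about 1.99 × 231 = 460.
- Interaction: under compound symmetry, SD = √2 × 2000 = 2828. At n = 75, SE = 2828/√75 = 327, with a half-width of about 651. At n = 30, SE = 2828/√30 = 516, with a half-width of about 1056.

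**Power for the interaction (noncentral t, two-sided 0.05)**

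| True interaction | n = 30 | n = 75 |
|---|---|---|
| 1250 | 65% | 97% |
| 800 | 32% | 68% |
| 625 | 22% | 47% |
| 500 | 16% | 33% |

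The 1250 is the plan's relevant difference for a control contrast. Using it for an interaction is an assumption, so smaller values are shown too.

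**What significance labels show when there is no interaction.** Four-condition data were simulated with purely additive effects, SD of difference 2000, n = 75 and paired tests at 0.0167. The last column is the share of trials in which fan alone is not significant and fan + wetting is.

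| Fan effect | Wetting effect | Share of trials |
|---|---|---|
| 0 | −1250 | 98% |
| −300 | −600 | 79% |
| −500 | −600 | 60% |
| −800 | −600 | 16% |
| +300 | −600 | 13% |
| −1250 | −600 | about 0% |

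The first row can be checked by hand. An inert fan is non-significant in 1 − 0.0167 = 98.3% of trials, and fan + wetting at −1250 has 99.8% power at n = 75. Their product is about 98%. In every row the interaction contrast at 0.05 is falsely positive in about 5% of trials. Apart from 1250, the effect sizes are illustrative and come from no document.

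**The case against.** The strongest reply is that the plan does what it says. The hypothesis in SAP 2.2 is control against each intervention, and the three contrasts match it exactly. A literature review may explain why a combination arm is included without binding the SAP to test the mechanism. This stands: there is no mismatch between hypothesis and primary test.

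The four-level model also loses nothing. It is already the saturated 2x2, and the interaction point estimate follows from the reported differences as (FW − C) − (F − C) − (W − C), where C is control, F fan, W wetting and FW both. That stands too, but the interval does not follow. It needs the covariance of the contrasts, which the SAP does not plan to report.

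Sydney protocol 4.7 has Holm-corrected paired t-tests that could include fan + wetting versus wetting. The pairs are not listed, and the SAP does not carry these tests over.

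Two stronger readings are tempting, and the documents support neither.
- A reader might infer that both protocols expect a fan alone to fail. At 38°C/60% RH both hypothesise that it beats control. The evidence of harm in older adults cited by Montreal comes from 42°C.
- A reader might infer that the authors will misread the pattern of significance. No text says so. How often the pattern arises under additivity depends wholly on the assumed effects, so no single figure from the table is a forecast.

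Factorial main effects could also be requested. They are not needed here: if an interaction exists, a fan main effect averages two different fan effects.

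**Conclusion.** The point holds as a low-cost improvement and is not a flaw in the primary analysis. The plan as written gives no interval or test for the fan's added effect on wet skin, or for whether wetting changes the fan's effect. The first bears directly on the objective of finding the best strategy; the second is the stated Montreal rationale.

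Under additive effects, the labels on the control contrasts would suggest that wetting makes the fan work in about 0% to 98% of trials, so they are no substitute. Sample size is no reason to leave the contrasts out of the pooled analysis: an interaction of 1250 has about 97% power at n = 75. Power falls to about 47% for 625, and is 65% for 1250 at n = 30. All of this rests on an SD of difference of 2000, compound symmetry and the assumed 75 completers.

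**What to change.** In SAP 5.2.1, keep the three primary contrasts and their 0.0167 level. From the same fitted model add:

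1. Fan + wetting versus wetting, with a 95% CI.
2. The fan by wetting interaction, (fan + wetting − wetting) − (fan − control), with a 95% CI.

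Label both secondary or exploratory. State that any claim that wetting changes the fan's effect rests on the interaction interval, not on which control contrasts are significant, and that a wide interval is not evidence of no interaction.

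In SAP 5.2.2, add the same two contrasts at 45°C/15% RH using Sydney participants only, since Montreal has no fan conditions there. Those Sydney visits are optional, so n is unknown and no power can be given.

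The cost is two contrast statements per exposure, restricted to Sydney in dry heat, and one paragraph. No new data are needed, and the primary test and its alpha do not change.

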### *2.2 Research hypotheses:*

The research hypotheses for this study are:

3. In the hot and humid condition, all interventions will result in improved cooling compared to the control (no-fan) trial. With fan and skin-wetting (FSW) being the most effective, then no fan and skin-wetting (NFSW), then fan (F), and finally, the control, no-fan (NF).
4. In the very hot and dry condition, skin wetting with no fan (SWNF) will be the most effective cooling intervention followed by fan and skin-wetting (FSW). We expect the fan (F) intervention to be less effective than the control, no-fan (NF).

*4.3 Participant characteristics:* To complete this study, 56 (greater than or equal to 60 years) adults will be recruited from previous participants who have consented to being contacted for future studies and through the distribution of recruitment flyers at both the Cumberland and Camperdown campuses at The University of Sydney.

*4.4 Sample size:* The sample size computation is based on comparison of the primary endpoint (change in rate pressure product from baseline to the end of a 2 h simulated heatwave exposure to 38°C and 60% relative humidity) between the 4 conditions of control, fan use alone, skin wetting alone, fan use + skin wetting. This preliminary data from young healthy participants was provided by [name], a former PhD student from within our laboratory. A non-repeated measures ANOVA on this data demonstrates 20% (eta squared of 0.2) of the variability was due to the intervention. Using GPower 3.1.9.2 software, an ANCOVA: Fixed effects, main effects and interactions f-test was performed using an alpha of 0.05, beta of 0.1 and an effect size of 0.5 to determine a total sample size of 45 is needed to obtain sufficient statistical power. To account for approximately 20% loss to follow up, 56 participants will be included in the study. Of the 56 participants, 14 will be healthy older females, 14 will be healthy older males, 14 will be healthy females taking antihypertensive medication, and 14 will be older males taking antihypertensive medication.

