#### 4.7 Statistical Analysis:

The primary research outcomes for this study are rectal temperature (Tre), rate pressure product (RPP), heart rate (HR), blood pressure (BP), thermal sensation (TS), thermal comfort (TC) and pre to post trial whole-body sweat losses (WBSL). Secondary outcomes to be compared are skin temperature (TSk), limb blood flow (LBF), skin blood flow (SkBF), local sweat rate (LSR), cognitive performance, rating of nausea and light headedness (NL), and evidence of orthostatic hypotension (OH). All data will be compared between all four interventions and both conditions (very hot and dry, and hot and humid). To assess the primary and secondary outcome variables, pre to post trial changes as well as the means of the dependent variables will be analyzed using one-way repeated measures ANOVAs with the repeated factor of cooling intervention (four levels: no fan (NF), fan (F), fan and skin-wetting (FSW), and no fan and skin-wetting (NFSW)) will be employed. If significant main effects or interactions are found, independent differences will be assessed using a two-tailed paired Student's t-tests while maintaining a fixed probability (5%) of making a type I error using a Holm-Bonferroni correction. All statistical analyses will be performed with GraphPad Prism (version 6.0, GraphPad Software, La Jolla, CA).

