## **2.2 Study Objectives**

### **Primary objective :**

The primary objective of this study is to identify the optimal cooling strategy to alleviate cardiovascular strain of participants exposed to typical North American heatwave conditions (38°C with 60% RH). Cardiovascular strain will be quantified using rate pressure product, calculated as heart rate × systolic blood pressure. To address this objective, we will test the following hypothesis: During simulated heatwave conditions of 38°C and 60% RH, a control (no intervention) condition will result in a greater increase in rate pressure product compared to conditions of: fan use alone; skin wetting alone; fan use + skin wetting.

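### The SAP sets out to identify the optimal cooling strategy but plans only comparisons with control, so choosing among strategies that beat control has no planned estimate, interval, test or rule

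*Supplement*

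**What the plan says.** SAP 2.2 opens with: "The primary objective of this study is to identify the optimal cooling strategy to alleviate cardiovascular strain of participants". The hypothesis offered to address this is narrower. It says that exposure without any cooling "will result in a greater increase in rate pressure product compared to conditions of: fan use alone; skin wetting alone; fan use + skin wetting". The secondary objective repeats the search for the best strategy at 45°C and 15% RH, with no hypothesis beneath it.

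SAP 5.2.1 fits a mixed model with a term for condition. It says "Contrasts under this model will allow for the three main comparisons" and lists fan, skin wetting, and fan + skin wetting, each against control. It then states: "Differences between the control condition and each of the 3 other conditions will be tested". Estimates come with 98.33% confidence intervals. On error control the section adds: "These three comparisons will be tested at the 0.0167 significance level to control for the multiplicity of tests". SAP 5.2.2 lists the same three contrasts at 45°C, with 95% intervals. SAP 5.2.3 treats the tertiary endpoints in the same way, and the beta-blocker, subgroup and season analyses add condition effects and interactions.

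The two protocols differ. Montreal protocol 6.2 has the same three control contrasts. Sydney protocol 2.2 ranks all four conditions in each climate. Its section 4.7 compares all four by paired t-tests "while maintaining a fixed probability (5%) of making a type I error using a Holm-Bonferroni correction". The SAP covers the combined data of both studies and carries over only the Montreal set.

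**The concern.** Calling one strategy optimal is a statement about differences between strategies. A contrast with control shows that a strategy works, not that it works better than another. A practical question here is whether a fan adds anything to wetting the skin, and the SAP plans no estimate or interval for it.

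Two outcomes leave the objective open. If two or three strategies beat control, nothing in the plan separates them. If some reach 0.0167 and others do not, a reader may take that pattern as a ranking, although a significant and a non-significant result against the same control do not show that the two strategies differ.

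**Working it through.** **1. Reproduce the plan's own figure.** Montreal protocol 6.1 gives a difference of 1250, SD of the difference 2000, and a paired t-test at two-sided 0.0167. With n = 30, df = 29 and noncentrality (1250/2000) × √30 = 3.42, power is 80.5%, and 30 is the smallest n that reaches 80%. Allowing 10% loss, 30/0.9 = 33.3, so 34. Both stated figures reproduce. The calculation concerns control-versus-strategy differences only.

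**2. Combined sample size (assumption).** The SAP states none. The protocols need 30 (Montreal) and 45 (Sydney) completers and enrol 34 and 56. That gives 30 + 45 = 75 to 34 + 56 = 90.

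**3. What the control contrasts would show if the three strategies were truly equal.** Simulation of the four-condition repeated-measures model, 20,000 runs per row, each contrast with control tested at 0.05/3. The correlation between conditions is assumed to be 0.5, so the SD of a difference is SD × √(2 × (1 − 0.5)) = SD. The effect of 1250 is the Montreal protocol's clinically relevant difference. The effect of 700 is the full spread of its expected mean changes (1700 − 1000). The SDs of 1700 and 2000 are its stated range.

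| n | Effect of each strategy | SD of difference | All three significant | Some but not all |
|---|---|---|---|---|
| 75 | 1250 | 2000 | 99.7% | 0.3-0.5% |
| 90 | 1250 | 2000 | 99.9% | 0.1% |
| 75 | 700 | 2000 | 51% | 40% |
| 90 | 700 | 2000 | 64% | 31-32% |
| 75 | 700 | 1700 | 74% | 24% |
| 90 | 700 | 1700 | 85% | 15% |

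Ranges reflect repeat runs. In the third row, the 40% splits into about 15% with exactly one significant strategy and 25% with exactly two. Only the former singles out one strategy.

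**4. What the missing contrasts could deliver.** Participants are meant to undergo all four conditions at 38°C, so the same model estimates the differences between strategies. With SD 2000:

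- The half-width of a 95% interval is t × 2000/√n, that is 460 at n = 75 and 419 at n = 90.
- The smallest difference with 80% power at 0.05/6 (all six pairs) is 823 at n = 75 and 748 at n = 90. At 0.05/3, the first Holm step in a family of three, it is 762 and 693.
- For a difference of 700 at 0.05/6, power is 63% to 73%. With SD 1700 it is 80% to 88%.
- For a difference of 300 at 0.05/6, power is 9% to 11%. With SD 1700 it is 13% to 16%.

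**The case against.** The strongest reply is that SAP 2.2 makes the objective operational through a control-only hypothesis. The contrasts in 5.2.1 test that hypothesis, and the Montreal sample size was built for it. That stands: tests and hypothesis agree, and the control comparisons are valid. It does not settle the point, because the hypothesis is narrower than the objective above it, and the 45°C objective has no hypothesis to narrow it.

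It can also be said that point estimates may be ranked descriptively and that the data can support further contrasts. Both are true, so this is a gap in the plan and not in the design. A ranking of estimates without intervals for their differences still carries no stated uncertainty.

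Three stronger readings are tempting and not supported:

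- *That the SAP ranks strategies by which contrasts reach 0.0167.* It contains no such rule. It reports estimates with intervals and is silent on selection.
- *That a mixed pattern is likely under the Montreal design and each one names a false winner.* At n = 30 and 1250, about 28-29% of trials are mixed. But n = 30 is one site, while the SAP pools two; at the assumed combined size the figure is 0.5% or less. Of the 28-29 points, only about 9 have exactly one significant strategy.
- *That the fixed 0.0167 is an error because Holm is more powerful.* It is a valid prespecified level that agrees with the 98.33% intervals and the sample size. Preferring Holm there is a matter of choice.

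**Conclusion.** The mismatch holds. Followed exactly, the SAP answers whether each strategy beats no intervention and leaves the question of which is best, at either climate, without a planned answer. The comparisons among strategies in one of the two source protocols were not carried into the combined analysis.

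The size depends on the true effects. With large, similar effects (1250 each), almost every trial ends with all three strategies superior to control and no basis for choosing. With moderate equal effects (700 each), 31-40% of trials at SD 2000 give a mixed pattern that could be misread, and 15-24% at SD 1700. These figures assume a combined n of 75 to 90, equal strategies, complete data and a correlation of 0.5.

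A reader might infer that the trial is unable to identify a best strategy. The documents do not support that: the 38°C data can estimate the contrasts, with useful precision for differences of about 750-820 and above. The change should be made, but the control comparisons are sound as they stand.

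**What to change.** In SAP 5.2.1, add three contrasts from the same mixed model: fan + skin wetting versus skin wetting, fan + skin wetting versus fan, and skin wetting versus fan. Make them key secondary, with estimates, confidence intervals and Holm-adjusted p-values in a family of their own. Leave the three control contrasts at 0.0167 with 98.33% intervals, so that they lose no alpha. State that a strategy will be called optimal only if these contrasts support it. If the sponsor does not want them, reword the objective as superiority of each strategy to no intervention.

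In SAP 5.2.2, report the same contrasts as estimates with 95% intervals only, in keeping with that section. All three involve a fan condition, and by SAP 2.1 only Sydney ran fan conditions at 45°C, in optional visits. They should therefore be estimated from Sydney participants, so that a Sydney-only condition is not set against one drawn from both sites.

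The cost is three more contrasts per climate, with no new data. Power at 38°C is limited for differences between strategies below about 750-820 (SD 2000, assumed n of 75 to 90, alpha 0.05/6), and a non-significant contrast must not be read as equivalence. Precision at 45°C will be lower.
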